#### 2- Pelvic floor muscle training

The patients in the PFMT group will be assisted during the sessions by an experienced physiotherapist ([name]). The participants of this group will have 12 individual sessions of supervised PFMT, lasting 40–60 minutes, once a week, and totaling 12 weeks of treatment and continue their treatment with home PFMT program. To follow the treatment at home, patients will receive a printed diary containing the complete PFMT program, with figures illustrating the positions and orientations for each exercise for the pelvic floor muscles. Patients will have the possibility to contact the physiotherapist for questions regarding home treatment by video call, audio call or messages through a telephone number made available exclusively for the study. Patients will be instructed not to perform other exercises for the pelvic floor, different from the exercises proposed by the intervention program of the present study. Our intervention program for PFMT is based on the studies of Bo *et al*. [37] and Dumoulin *et al*. [38].

*2*.*1- Procedure*. The first PFMT session is longer and focused on the careful evaluation of the pelvic floor muscles in order to identify any muscle condition that interferes with the progress of the intervention; guidance on the correct performance of the pelvic floor muscle contraction with the aid of vaginal palpation and educational material; presentation of the PFMT program; and finally, the first sequence of exercises.

Patients will be instructed to perform three phases of exercise in each session, with at least two sessions of the PFMT program per day (Table 1). The exercises will undergo progression every 4 weeks of intervention, totaling three progressions (6 repetitions, sustained for 6 seconds, 6 seconds for rest, 8 repetitions, sustained for 8 seconds, 8 seconds for rest, and 10 repetitions, sustained for 10 seconds, 10 seconds for rest). The first phase comprises three exercises of maximum contraction of the pelvic floor muscles in the supine position, with the lower limbs semiflected and the feet supported, associated with contraction transverse exercise, and hip elevation. The second phase comprises pre-contraction of the pelvic floor muscles associated with cough; maximum sustained contraction in the supine position with the lower limbs extended and abducted; fast contractions in both supine and sitting positions, contraction in three stages (mild, moderate, maximum) in a sitting posture; maximum sustained contraction in standing posture and four supports (hands and knees). The third phase comprises the relaxation period with breathing exercises associated with pelvic mobilization in a standing posture. No pelvic floor muscles contraction in this phase. Patients will be instructed on the importance of adhering to the PFMT. In case of two absences, the patients will be contacted and their permanence in the study will be reassessed.

### Primary outcomes

The primary outcome will be the indication of improvement in the VL symptoms after the proposed interventions assessed through a single question with seven possible answers. The Global Response Assessment (GRA) [2] is a 7-level scale with response to the question: “How are you now (levels of vaginal laxity/tightness and sexual satisfaction) compared to before treatment” (markedly improved, moderately improved, slightly improved, no change, slightly worse, moderately worse, markedly worse?). This scale item has been already used to evaluate improvement in vaginal laxity symptoms after treatment [2].

### Secondary outcomes

The description of secondary outcomes is described below together with their measurement instruments.

Female Sexual Function Index (FSFI) [39]: a brief and multidimensional instrument to assess sexual function in women. The questionnaire was developed and validated by Rosen *et al*. and consists of 19 items that investigate sexual response over the past four weeks and performance in six domains: sexual desire, arousal, lubrication, orgasm, satisfaction, and pain [39]. The validation in Portuguese took place in 2008 by Thiel *et al*. [40]. The answers are scored according to the sum of the items that make up each domain (simple score) and multiplied by the domain factor generating the weighted score [40]. The maximum score is 36 points, adding up the total of each domain. Wiegel *et al*. proposed a cut-off score to differentiate women with or without sexual dysfunction in the amount of 26.55 [41].

Female Sexual Distress Scale-Revised (FSDS-R): a self-report questionnaire with 13 questions scored on a 5-point Likert scale from 0 (never) to 4 (always) to assess the sexual distress. Sexual distress is characterized by a set of feelings (for example, unhappiness, guilt, frustration, stress, worry) and emotions that individuals have about their sexuality. It differs from sexual dysfunction related to symptoms of sexual function, such as arousal, orgasm and pain, separate from emotions [42]. The Portuguese translation was developed by Berenguer *et al*. [43].

International Consultation on Incontinence Questionnaire—Vaginal Symptoms (ICIQ-VS): is a 14-item questionnaire validated for the Portuguese language by Tamanini *et al*. that assesses the presence and the impact of vaginal symptoms, as well as their relationship with quality of life [44, 45].

International Consultation on Incontinence Questionnaire Short-Form (ICIQ-SF): validated in Portuguese by Tamanini *et al*., is a simple, brief, and self-administered questionnaire, capable of quickly and effectively assessing the impact of urinary incontinence on patients’ quality of life. It consists of four questions that assess the frequency, severity, and impact of urinary incontinence. Your score can vary from 0 to 21, the greater the commitment, the higher the total value [46, 47].

Pelvic Organ Prolapse Quantification (POP-Q): the ICS recommends POP description and staging using this instrument [48, 49]. The staging classification is defined as [50] Stage 0: there is no demonstrated prolapse; Stage I: the most distal part of the prolapse is more than 1 cm above the level of the hymen; Stage II: the most distal portion of the prolapse is between 1 cm above the hymen and 1 cm below the hymen; Stage III: the most distal portion of the prolapse is more than 1 cm beyond the plane of the hymen, but everted at least 2 cm less than the total vaginal length; Stage IV: complete eversion or eversion of up to 2 cm from the total length of the lower genital tract. The hymen is the reference point used to describe the quantitative prolapse and represents the zero point. Six anatomical points will be evaluated with the aid of a disposable graduated ruler. Two on the anterior vaginal wall (Aa and Ba). Two on the posterior vaginal wall (Ap and Bp) and two points on the upper vagina (C and D). The genital hiatus, the total vaginal length and the perineal body will also be measured. All points will be measured in Valsalva maximum, except the total vaginal length [50]. The ICS clinically defined significant POP in stage II or higher [49, 50].

Pelvic Floor Muscle Strength (PFMS): the strength of the pelvic floor muscles will be graduated according to the modified Oxford scale (5-point) by means of bi-digital vaginal palpation with the patients in the supine position with the lower limbs supported [35].

Pelvic Floor Muscle Morphometry (PFMM) and Vaginal Thickness (VT): the morphometry of the pelvic floor muscles will be assessed during rest, during contraction of the pelvic floor muscles, and during the Valsalva maneuver [51]. The vaginal thickness will be assessed in its proximal, middle, and distal third using two approaches—transabdominal and transvaginal [52, 53]. The equipment used for transabdominal, transvaginal and transperineal ultrasound measurements will be the GE Voluson 730 Expert® (GE Medical System Kretz-Technik GmbH and Co OHG, Zipf, Austria). The 2 to 6 MHz convex RAB4-8L 3D / 4D probe will be used to record the morphometry of the pelvic floor muscles. Measurements will be performed at rest, Valsalva maneuver, and pelvic floor muscle contraction with the patient in the supine position [51] for the angle of the levator plate, the anorectal angle, the thickness of the levator ani muscle, and the area of the levator hiatus in cm^2^. For vaginal thickness, probes 4C-D 2 at 5 MHz transabdominal and 5 to 9 MHz transvaginal will be used to measure the vagina in its proximal, middle, and distal thirds [52, 53].

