To our knowledge, to date, no clinical trial has been developed to assess the role of pelvic floor muscle and radiofrequency training in VL. Thus, the general objective will be to compare the effect of RF and PFMT in women with VL symptoms. The specific objectives are related to the assessment of the sexual function, vaginal symptoms, and sexual distress, as well as, to assess the impact of UI on patients’ quality of life. The POP staging, contractility, and pelvic floor muscle function will be also evaluated. Finally, we will assess the impression of improvement in VL complaints after the interventions.

Our hypothesis is that RF will be different from PFMT in treating women with VL symptoms.

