### Eligibility criteria

We will include women aged ≥ 18 and ≤ 60 years, with VL complaints assessed by direct question (yes / no) and by the VLQ [2] (very loose, moderately loose, slightly loose), and willing to attend treatments on the scheduled date and places.

Participants who present the following conditions will be excluded from the study: use of a pacemaker; decompensated heart disease; cognitive deficit; peripheral or central neurological disorders; the presence of any type of cancer; the presence of cervical dysplasia; history of active urinary or vaginal infection; decompensated metabolic diseases; patients undergoing physical therapy for pelvic floor disorders; patients using vaginal estrogen in the last 6 months; patients already undergoing surgery for prolapse or urinary or anal incontinence; patients with stage 2 POP onwards; force of contraction of the pelvic floor muscles equal to zero according to the modified Oxford scale [35].

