### Data analysis

Initially, a descriptive analysis of the data will be performed to characterize the research participants, in the form of values ​​of absolute frequency and percentage (relative) for categorical variables and values of mean and standard deviation for numerical variables.

Statistical analysis of comparison and correlation of the obtained data will be performed. The Kolmogorov-Smirnov test will be performed to analyze the sample’s normality. Depending on the results obtained in the normality test, the Analysis of Variance (data with normal distribution) or Wilcoxon and Mann-Whitney Test (non-parametric data) will be used for comparative analyzes between the groups. Likewise, Pearson or Spearman tests will be used for correlational analyzes. Categorical variables will be analyzed using the chi-square test or Fisher’s exact test. Statistical analyzes will be performed using the statistical program SAS System for Windows (Statistical Analysis System), version 9.4, adopting a significance level of 5% (p <0.05). Study endpoints will be analyzed primarily for the per protocol population, and repeated, for sensitivity reasons, for intention-to-treat population [54].

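### ICIQ-SF is compared in whole groups although incontinence is not an entry criterion, so women scoring 0 at baseline dilute the comparison by an amount the protocol does not let one size

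*Protocol article*

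**What the plan says.** The Introduction of the protocol article lists among its specific objectives "to assess the impact of UI on patients" and their quality of life. The instrument is ICIQ-SF, described under Secondary outcomes: "Your score can vary from 0 to 21, the greater the commitment, the higher the total value".

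Under Eligibility criteria, women enter "with VL complaints assessed by direct question (yes / no) and by the VLQ". UI is not required, and nothing excludes continent women. The two exclusions closest to the topic, "patients already undergoing surgery for prolapse or urinary or anal incontinence" and "patients undergoing physical therapy for pelvic floor disorders", remove some women treated for pelvic floor problems and no continent women as such.

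The Follow-up period assessment section repeats the baseline questionnaires at both visits for everyone. In the Data analysis section, analysis of variance or rank tests "will be used for comparative analyzes between the groups", with the per-protocol population first and intention to treat as the sensitivity analysis. That section names no subset by baseline UI, no handling of scores at the floor and no baseline adjustment for ICIQ-SF. The Baseline assessment section shows that the questionnaires and urinary habits are recorded at the first visit. Under Allocation, the envelope is opened after that assessment.

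**The concern.** The lowest ICIQ-SF score is 0. A woman who starts there can stay or worsen but cannot improve. If a sizeable share of the sample is continent, the whole-group comparison averages the effect in women who have the problem with a block of women in whom no benefit can be measured.

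This matters here because the Introduction and the Trial design section describe pelvic floor muscle training as first-line treatment for UI, so ICIQ-SF is an outcome on which the arms could plausibly differ. The Discussion looks ahead to the two therapies proving equally effective. A null ICIQ-SF result produced partly by dilution could be taken as support for that on UI.

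**Working it through.** **Inputs from the protocol.** 34 women per group including 30% loss; two-sided 5% level; ICIQ-SF range 0 to 21. After the planned loss, 34 × 0.7 = 23.8, or about 24 evaluable per arm.

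**The plan's own figure.** The 34 per group rests on FSFI (7 − 3 = 4 points). No SD is given, so it can be neither confirmed nor refuted. With n/(1 − 0.3), it implies an SD of about 4.8 to 4.9. It does not bear on ICIQ-SF.

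**Not in the documents, so assumed.** The UI share p; the ICIQ-SF effect and SD among women with UI; how many continent women develop leakage.

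**Step 1: dilution.** Let D be the between-arm difference in mean change among women with UI, and E the same difference among women scoring 0 at baseline. Then

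D_all = p × D + (1 − p) × E.

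If women at 0 stay at 0, E = 0 and D_all = p × D. Take a 4-point shift, which becomes about 3.5 points once the floor is respected:
- p = 0.3: 0.3 × 3.5 = 1.05
- p = 0.5: 0.5 × 3.5 = 1.75
- p = 0.7: 0.7 × 3.5 = 2.45

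**Step 2: does restricting pay, given fewer women?** Work in SD units of change among women with UI. Take D = 0.825, which is 4/4.85, about the standardised effect implied by the FSFI calculation. With mean change m in an arm, the variance of the mixture is p(1 + m²) − (pm)². At p = 0.5 and 24 per arm:
- Comparator change 0: variances 0.500 and 0.670, pooled SD 0.765, standardised difference 0.4125/0.765 = 0.54. Then 0.54 × √12 − 1.96 ≈ −0.09, power 0.46.
- Comparator change 1 SD: variances 0.750 and 1.333, pooled SD 1.020, standardised difference 0.40, power 0.29.
- Subset of 12 per arm: 0.825 × √6 − 1.96 = 0.06, power 0.52.

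The same calculation over the assumed range, 24 per arm (all-women range: comparator change 1 SD to 0):

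| UI share | Difference, all women (SD) | Power, all women | Power, subset |
|---|---|---|---|
| 0.8 | 0.66 | 0.57 to 0.70 | 0.72 |
| 0.6 | 0.495 | 0.37 to 0.55 | 0.60 |
| 0.5 | 0.41 | 0.29 to 0.46 | 0.52 |
| 0.4 | 0.33 | 0.22 to 0.38 | 0.44 |
| 0.3 | 0.25 | 0.17 to 0.29 | 0.35 |

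**Step 3: Mann-Whitney simulation on the ICIQ-SF scale.** Among women with UI: baseline mean 9 (SD 4), a 4-point difference in shift, within-woman change SD of about 4. Continent women stay at 0. UI share 50%; power in all women against power in the subset:
- 34 per arm, comparator static: 62% to 66% against 73%.
- 34 per arm, both arms improving: about 45% against 65%, depending on how far the comparator improves.
- 24 per arm, comparator static: 51% against 57% to 59%.

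With a static comparator the gap is 7 to 11 percentage points at 34 per arm and 6 to 8 at 24.

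**Step 4: new leakage.** Let 20% of continent women in the worse-performing arm and 5% in the other develop leakage, so that E has the same sign as D. At 24 per arm, all women against subset: 48% against 32% at p = 0.3, 57% against 56% at p = 0.5, and 74% against 76% at p = 0.7. The ranking reverses at the low share and is level at the middle one.

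**The case against.** The strongest reply is that the all-women comparison is a legitimate target. The trial treats women with vaginal laxity, and the average effect on ICIQ-SF in that population answers a real question. It also captures new leakage. That stands. A reader might infer that the planned comparison is biased or invalid, and the documents do not support this: under intention to treat it is an unbiased estimate of a population average.

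A second reply is that a subset for one secondary questionnaire belongs in an analysis plan that is not shown. This has some force, but the Data analysis section does more than stay silent: it fixes the populations and the type of test for the study endpoints, and those choices suit this objective poorly.

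Third, the size is entirely assumed. That also stands. Recruitment is partly from a urogynecology clinic, which could mean a high UI share, and partly through social media and other advertising, which could mean a lower one. No particular loss of power can be claimed as the trial's own.

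Two further inferences go too far. The protocol does not say that unadjusted follow-up scores will be compared; it leaves open whether change or follow-up score is used. Nor is a baseline-defined subset protected by randomisation in every population. Per protocol is the primary analysis, and the Harms section discontinues women on attendance rules that differ by arm, so a per-protocol subset is selected after randomisation.

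**Conclusion.** The point holds as a design weakness in one secondary outcome. UI is not required for entry, ICIQ-SF is given to all women, its floor is 0, and the stated comparison is between whole groups, so the difference bearing on the UI objective shrinks roughly in proportion to the UI share. That proportionality assumes that women at 0 stay there or worsen equally in both arms.

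The direction is fairly robust. Without differential new leakage, the subset had higher power at every assumed UI share below 1, despite fewer women. The amount is not known. If nearly all participants have UI, the dilution is small; if new leakage differs by arm, the all-women comparison may be the more powerful one. The power figures are illustrations for unadjusted comparisons of change, not estimates for this trial or for the adjusted analysis proposed below. The primary outcome (GRA) and the FSFI-based sample size are untouched.

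**What to change.** In the Data analysis section, add that:
1. ICIQ-SF is compared between arms among women with a baseline score above 0, adjusted for baseline score, in all randomised women of that subset (intention to treat). The per-protocol version may be shown but should not carry the conclusion.
2. Among women scoring 0 at baseline, new UI (a follow-up score above 0) is reported by arm as counts.
3. The all-women comparison is kept, adjusted for baseline ICIQ-SF.

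The cost is a few lines of analysis text and no new data, since baseline ICIQ-SF is already collected before allocation is revealed. The downside is that the subset comparison uses fewer women and applies only to women with UI at entry. As recruitment has begun, the rule should be fixed before any outcome data are examined by arm, so that the subset cannot appear to have been chosen from the results.

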### Baseline assessment

After signing the consent form, patients will be submitted to an anamnesis that includes questions related to the date of birth, marital status, ethnicity, education, body mass index, physical activity, surgeries, prior diseases, and medication. Questions related to sexual life such as sexual activity (yes / no), type of sexual behavior (homosexual, heterosexual, bisexual), type of sexual intercourse (vaginal, anal or both), origin of VL complaint (participant, partner or both), time of VL symptoms (months). In addition, patients will be asked about their perception of VL symptoms. Questions related to obstetric history and urinary / intestinal habits will also be included.

Subsequently, patients who sign the consent form will be referred for a physical examination consisting of the assessment of the strength of the pelvic floor muscles and POP quantification. The questionnaires will be self-completed by the participants and collected at the end of the baseline assessment. Patients will then be referred for ultrasound exams. These procedures will be performed in the initial assessment (first visit).

### Follow-up period assessment

Patients will be followed up in two periods after the interventions: first follow-up (30 days after intervention) and second follow-up (six months after intervention). The assessment procedures in the follow-up period will be the same as those used in the baseline physical examination, questionnaires, and ultrasound exams. We will add the Global Response Assessment.

### Data collection and management

Researchers with over 20 years of research experience will coordinate data collection. An assistant researcher will be responsible for checking all signatures of the consent form and the answers to each questionnaire to ensure that there is no blank answer. A researcher will perform a physical examination of all patients in the study. An experienced physiotherapist (over 10 years) and specialist in women’s health, under the supervision of the main researchers, will carry out both the interventions and different researcher with experience and expertise in ultrasound will perform the ultrasound exams. Patients will be contacted and monitored by telephone.

The analysis of the collected data will be preceded by the elaboration of a computerized database where the variables will be coded in a data dictionary and validated. This database will often be filled in by an assistant researcher and supervised by the main researcher.

### Harms

The suspension of the intervention will occur through the verification of significant levels of discomfort during the application of vaginal RF (Visual Analogue Scale), as well as the significant occurrence of events such as urinary tract infection, vulvovaginitis, irritation and vaginal injury after application of vaginal RF (telephone contact). In these cases, an appropriate medical treatment will be offered. Women will be discontinued if they miss any radiofrequency sessions or if their presence in physiotherapy sessions does not reach 80%.

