**Fig 1 pone.0259650.g001:**
[figure not shown]
Description of the study steps. F1: Follow-up (30 days after intervention); F2: Follow-up (6-months after intervention); w: week; PFMT: Pelvic Floor Muscle Training; BMI: Body Mass Index; ICIQ-VS: International Consultation on Incontinence Questionnaire—Vaginal Symptoms; ICIQ-SF: International Consultation on Incontinence Questionnaire Short-Form.

The term VL was recently defined and little is known about this complaint. There is still no gold standard treatment for VL and further studies are needed to understand its pathophysiology. Although its pathophysiology is not completely known, there is a consensus on the association of VL with pregnancy and childbirth [2, 10, 27]. Some proposed mechanisms involve overstretching of the vaginal walls and introitus during vaginal birth and an increase in levator ani hiatal dimensions resulting from macro and microtrauma of the levator ani muscle [7, 17]. Although supervised PFMT is recommended as a first-line treatment for stress or mixed UI in women by most of the guidelines [28–30], more studies are needed to demonstrate the effect of PFMT on female sexual function. A randomized controlled trial concluded that women reporting improvement in sexual function demonstrated greatest increase in PFM strength and endurance [31].

Regarding RF, a recent randomized, multicenter, sham-controlled clinical trial found a statistically significant and clinically important improvement of VL with RF when compared with Sham treatment [32]. In our study, RF will be applied once every 4 weeks (a total of three applications) and will probably be less likely to face problems related to treatment adherence when compared to PFMT. Although the RF procedure has been shown to be well tolerated, adverse effects may occur [32, 33]. PFMT is generally free of adverse effects.

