The device will be calibrated in FRAXX mode, 45 Watts, Low (initial application) and Medium (second and third application) Energy program (40 and 60 milliseconds, respectively), and the fractional vaginal electrode will be used. Applications will be under direct view. The electrode will be lightly pressed against the mucosa, without pressing, so that all microneedles are in uniform contact with the tissue. The application will be carried out sequentially on the lateral vaginal walls, in rows, avoiding overlapping, starting from the proximal third of the vagina to the distal third in the vestibule exposed by the opening of the speculum. The speculum will be gently rotated to the anteroposterior position for the application of the anterior and posterior vaginal walls. At the end of the procedure, the speculum will be gently removed. Patients will be advised on post-treatment care and the use of 5% dexpanthenol cream in the vaginal opening is recommended two to three times daily if there is any discomfort in the region for 2 to 3 days and interrupt sexual intercourse for 10 days. Patients will be instructed to contact the researchers if they experience any discomfort or notice any changes in vaginal discharge. These patients will be evaluated by an experienced gynecologist. There will be three vaginal applications at 4-week intervals, totaling 12 weeks of treatment.

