## Discussion

Vaginal laxity is a complaint that is still little discussed among patients and their physicians and the lack of evidence-based treatment negatively impacts the management of this condition. There is a need to evaluate non-surgical options that offer minimal adverse effects at lower costs for women with VL complaints.

The present study aims to investigate two types of non-surgical treatment for VL and to compare the effect of both therapies. If therapies prove to be equally effective for VL complaints, our study will open a path for non-surgical options for VL management. In addition, while we await evidence on the VL pathophysiology, our study will contribute to developing knowledge of treatment options for this condition that negatively affects women’s sexual lives and relationships.

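### Adverse-event enquiry is written out for the radiofrequency arm only, so any reading of harms by arm would be open to ascertainment bias against radiofrequency

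*Protocol article*

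**What the plan says.** All references are to the protocol article.

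- **Harms.** The section opens with a suspension rule: "The suspension of the intervention will occur through the verification of significant levels of discomfort" during RF. The discomfort part reads "significant levels of discomfort during the application of vaginal RF (Visual Analogue Scale"). It then adds "events such as urinary tract infection, vulvovaginitis, irritation and vaginal injury after application of vaginal RF (telephone contact"). The section also says that treatment will be offered in these cases and sets attendance limits. It mentions no event or enquiry for PFMT.
- **Interventions, Radiofrequency.** After each application: "Patients will be instructed to contact the researchers if they experience any discomfort or notice any changes in vaginal discharge". Women who do so are assessed by a gynecologist.
- **Interventions, Pelvic floor muscle training.** The stated contact route is for questions about the exercises: "Patients will have the possibility to contact the physiotherapist for questions regarding home treatment by video call, audio call or messages". Supervised sessions take place weekly for 12 weeks.
- **Trial design.** The rationale notes that RF may cause adverse effects, and continues: "PFMT is generally free of adverse effects".
- **Data collection and management.** One sentence is not limited to an arm: "Patients will be contacted and monitored by telephone". It gives no content, events or timing.
- **Follow-up period assessment.** Both arms have the same examination, questionnaires and ultrasound at 30 days and six months after the intervention.
- **Outcomes and Data analysis.** Harms are neither a primary nor a secondary outcome, and no test of harms between arms is named.

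**The concern.** A randomised comparator can show how many of the events seen after RF would have happened anyway. Three of the four listed events (urinary infection, vulvovaginitis, irritation) also occur in women who never receive RF. The PFMT arm supplies their background rate only if the same events are sought there in the same way. The article describes two ways of finding them after RF, a telephone contact and an instruction to report, and none for PFMT.

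The Discussion motivates the trial by a need for "non-surgical options that offer minimal adverse effects at lower costs", and the rationale contrasts the two treatments on adverse effects. Readers of the results are therefore likely to set the two arms' event counts side by side, with or without a test. If one arm was asked and the other was not, the difference mixes treatment effect with intensity of asking.

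**Working it through.** The article gives no figure on harms, so there is nothing to reproduce. The check has two parts.

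**1. Ascertainment as written, by arm**

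| Element | RF | PFMT |
|---|---|---|
| Named events | Four (Harms) | None stated |
| Telephone contact tied to those events | Yes (Harms) | None stated |
| Instruction to report symptoms | Yes (Radiofrequency) | None stated; contact offered for exercise questions |
| Discomfort scale during the procedure | Yes (Harms) | Not applicable |
| General telephone monitoring | Yes, content not given | Yes, content not given |
| Clinic contact during the 12 weeks | 3 applications | 12 weekly sessions, no harms question stated |
| Examination, questionnaires, ultrasound at 30 days and six months | Yes | Yes |

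The first three rows differ by arm in what is written. The general monitoring and the follow-up visits are common to both, but the article attaches no adverse-event question to either. Both follow-up visits come after the 12 weeks, so a brief infection or irritation that had resolved by then could be missed.

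**2. How much unequal detection could matter (illustration)**

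From the article: n = 34 per arm (Sample size), and Fisher's exact test at 5% as one of the tests for categorical variables (Data analysis). Assumed, because the article gives neither: the true risk *p*, equal in both arms, and the share of events detected, *d*, set at 0.90 in RF and varied in PFMT.

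Expected recorded events = 34 × *p* × *d*. Apparent risk ratio = *d*(RF) / *d*(PFMT). The false-positive probability is the sum of the binomial probabilities of all pairs of counts for which the two-sided Fisher p is below 0.05.

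At *p* = 0.20, RF expects 34 × 0.20 × 0.90 = 6.1 recorded events:

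| PFMT detection | PFMT expected | Apparent risk ratio | False-positive probability |
|---|---|---|---|
| 0.90 | 34 × 0.20 × 0.90 = 6.1 | 1.0 | 2.4% |
| 0.60 | 34 × 0.20 × 0.60 = 4.1 | 1.5 | 5.3% |
| 0.30 | 34 × 0.20 × 0.30 = 2.0 | 3.0 | 18.8% |
| 0.10 | 34 × 0.20 × 0.10 = 0.7 | 9.0 | 40.6% |

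Over the same range of PFMT detection, the false-positive probability runs from 1.0% to 5.9% at *p* = 0.10 and from 2.6% to 73.9% at *p* = 0.30.

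The extreme case is complete detection in RF and none in PFMT. Fisher p is 0.053 for 5/34 against 0/34 and 0.025 for 6/34 against 0/34, so six RF events are needed. At true risks of 5%, 10% and 15% the expected RF counts are 34 × 0.05 = 1.7, 34 × 0.10 = 3.4 and 34 × 0.15 = 5.1. The chance of six or more is 0.6%, 12% and 40%.

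So a spurious significant result is unlikely if these events are rare. The distorted risk ratio does not depend on how rare they are.

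**The case against.** The strongest reply is that the Harms sentence is a suspension rule for an RF procedure. Such a rule naturally speaks of RF, and it does not say that PFMT women go unasked. The telephone monitoring under Data collection and management is not restricted to an arm, and the wording of calls and event forms is what a journal article leaves to the full protocol. PFMT women are seen more often than RF women during treatment. Both arms are examined and complete the 14-item vaginal symptoms questionnaire (ICIQ-VS) at both follow-ups.

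Much of this stands, and it rules out three stronger readings that a reader might infer.

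- *Harms are sought only after RF.* Not established. The general telephone monitoring may ask both arms the same questions; the article does not say.
- *A planned comparison of harms is biased.* No such comparison is stated. The sentence in the Discussion about minimal adverse effects describes a need in the field and sets no objective.
- *Treatment harm cannot be told apart from background events.* Too strong, given the shared follow-up examinations and questionnaire and the weekly PFMT contact.

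Nor is the remark that PFMT is generally free of adverse effects an instruction not to ask.

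The reply does not remove the asymmetry. The Harms section is the only place that names events and says how they are found, so its data are likely to become the harms data, and the RF procedure text adds a second route for that arm alone. General monitoring without named events does not extend the list to PFMT, and weekly sessions are an opportunity to ask, not a stated enquiry.

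**Conclusion.** The point holds as a fault in how ascertainment is specified. The article writes out event enquiry for RF and states no matching enquiry for PFMT. If staff follow the text, background infections and irritation will tend to be recorded more completely in RF, and any by-arm reading of harms would be tilted against it.

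The size cannot be fixed from the article, because it rests on event and detection rates that are not given. With equal detection there is no bias. With detection of 90% against 30%, the apparent risk ratio is 3.0 at any equal true risk, and the chance of a false significant difference at 34 per arm is 18.8% if the true risk is 20%. These are assumed values. No stated efficacy analysis is affected. This is an inexpensive improvement worth making, not a flaw that undermines the trial's main comparison.

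**What to change.** State in the Harms section that both arms are asked the same checklist (urinary tract infection, vulvovaginitis, irritation, vaginal injury) at the same study weeks during the 12-week intervention and at both follow-up visits. Use the telephone contacts already described under Data collection and management and the existing visits. Putting the question at matched weeks, and not at whichever visit each arm happens to have, keeps the 12 PFMT sessions and 3 RF applications from creating a new imbalance. Give both arms the same instruction to report symptoms between contacts.

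Report the number of women with at least one event by randomised arm, with the difference and its 95% confidence interval. Recruitment is under way, so record the date from which the checklist applies.

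Discomfort during the RF application belongs to that procedure and need not be matched. The suspension rule is left as it is.

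Cost: a few minutes per contact and an amendment through the route the article already describes. No extra staff, visit or procedure is needed.
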